# Effects of a Monophasic Hormonal Contraceptive With Norgestimate+Ethinyl Estradiol on Menstrual Bleeding: Protocol and Design of a Multicenter, Prospective, Open-Label, Noncomparative Study in Italy

**DOI:** 10.2196/63683

**Published:** 2025-03-31

**Keywords:** combined oral contraceptive, ethinyl estradiol, menstrual cycle, monophasic, norgestimate, hormonal contraceptive, menstrual health, Italy, women’s health, patient-reported outcomes, methodology, observational study, reproductive health, data analysis, assessment

## Abstract

**Background:**

Norgestimate (NGM) is a progestin with negligible androgenic activity that is available in combination with ethinyl estradiol (EE) as a monophasic combined oral contraceptive (COC). It has been more than 30 years since a clinical study evaluated the effects of monophasic NGM/EE on menstrual cycle characteristics in healthy women, and in the interim, there has been growing recognition that clinical trials of contraceptives should evaluate a wide range of potential positive and negative impacts for users.

**Objective:**

The aim of this study is to investigate menstrual cycle control during the use of a monophasic COC formulation containing NGM 0.25 mg and EE 0.035 mg (Effimia; Italfarmaco SpA), using established methodologies as well as patient-reported outcomes.

**Methods:**

This is a prospective observational study being undertaken in a target population of 228 healthy Italian women aged 18-35 years who are starting oral contraception for the first time or switching from another COC. The participants are asked to complete a diary for 6 cycles recording information about their menstrual cycles (frequency, duration, regularity, estimated flow volume, and breakthrough bleeding), any unscheduled bleeding, and an evaluation of dysmenorrhea, using a 100-mm visual analog scale from 0=no pain to 100=very severe pain, and any adverse events. Compliance is assessed after 3 and 6 months via returned medication. The primary end point is the change from baseline in the rate of intermenstrual bleeding during the sixth cycle. At baseline, 3 months, and 6 months, acne will also be assessed using the Global Acne Grading Scale, and participants will complete a Profile of Mood State to assess premenstrual syndrome and the Female Sexual Function Index to evaluate the quality of their sex life. A subgroup of 28 participants at 1 site (Genoa) is also providing a blood sample for the assessment of metabolic, endocrine, and coagulation parameters.

**Results:**

Study enrollment began in July 2023 and is expected to be complete by December 2024. Data analysis is expected to be complete by October 2025.

**Conclusions:**

This study into the effects of monophasic NGM/EE 0.25/0.035 mg on menstrual characteristics in healthy Italian women will provide up-to-date data on these effects and includes assessments of a range of other parameters, such as acne severity and patient-reported outcomes, in line with recent international consensus recommendations.

**Trial Registration:**

ClinicalTrials.gov NCT06067256; https://clinicaltrials.gov/study/NCT06067256 and EudraCT 2021-003027-15; https://www.clinicaltrialsregister.eu/ctr-search/trial/2021-003027-15/IT

**International Registered Report Identifier (IRRID):**

DERR1-10.2196/63683

## Introduction

Combined oral contraceptives (COCs) are the most commonly prescribed form of hormonal contraception in Italy and in other European countries [1]. These contraceptive pills contain a combination of estrogen and progestin to suppress ovulation (the primary contraceptive effect) and to change endometrial and cervical secretions, hindering the passage of sperm [2]. COCs may be monophasic or multiphasic. Monophasic COCs contain the same dose of estrogen and progestin in each pill, whereas the ratio of these hormones varies over the course of a cycle in multiphasic COCs.

Since the first development of COCs in the 1960s, formulations have been modified to reduce the risk of undesirable adverse events (AEs) and cardiovascular health risks [3]. The early progestins used in first- and second-generation COCs were chemically related to testosterone and caused androgenic AEs such as acne, hirsutism, and oily skin, which could undermine adherence as well as negative effects on high-density lipoprotein cholesterol [4]. Newer progestins have been structurally modified to be less androgenic or are structurally related to spironolactone [5,6]. In addition, estrogen doses have been progressively lowered, and most COCs in use today contain ≤0.035 mg of ethinyl estradiol (EE) [3]. COCs containing the first- and second-generation progestins were associated with a markedly higher risk of venous thromboembolism (VTE) compared with COCs containing the newer-generation progestins [7].

One such newer-generation progestin is norgestimate (NGM). NGM is a third-generation progestin derived from 19-nortestosterone [8]. It is rapidly hydrolyzed in vivo to norelgestromin, the primary active metabolite (75% to 80%), and levonorgestrel (20% to 25%) [9]. Both NGM and its metabolites have activity similar to endogenous progesterone but have a very poor affinity for androgen receptors and are therefore less androgenic than earlier progestins such as norgestrel, gestodene, or levonorgestrel [9,10]. In addition, unlike levonorgestrel, NGM increases levels of sex hormone–binding globulin in plasma, but does not bind to sex hormone–binding globulin, and is associated with reduced levels of free testosterone [11]. Data show that COCs containing NGM carry a lower risk of VTE than COCs containing cyproterone acetate, desogestrel, dienogest, drospirenone, or gestodene [12,13]. On the other hand, contraceptive patches containing norelgestromin are associated with a slightly higher incidence of VTE compared with levonorgestrel-containing COCs, presumably because of the high cumulative dose of EE that accompanies the transdermal route of administration [9].

Women want their contraceptives to be effective in preventing pregnancy, convenient, safe, and well tolerated, and with excellent cycle control [14]. Unscheduled bleeding has a number of negative impacts on a woman’s life, in addition to the inconvenience, including the potential for a negative effect on their sexual life and confusion about the status of their cycle [14]. Some women may interpret unscheduled bleeding as an indication that the COC is not working or interrupt use because of it [14]. Monophasic COCs containing 0.030-0.035 mg of EE offer women the greatest likelihood of a regular bleeding pattern with a low risk of estrogen-associated risks as well as the option of fewer periods by reducing or eliminating the placebo period altogether [15]. As well as preventing pregnancy and potentially providing better cycle control (increased regularity and reduced intermenstrual bleeding), COCs may also offer improvements in acne and premenstrual or menstrual symptoms, such as mood changes, headaches, and pelvic pain [16]. However, effects on these parameters vary between COCs [16].

A large German study (N=59,701) demonstrated that the use of a monophasic COC containing 0.25 mg of NGM and 0.035 mg of EE reduced the rate of breakthrough bleeding in healthy women compared with the rate before they started taking NGM/EE [17]. Similar results were seen in an Italian study among 92 women receiving NGM/EE [18]. However, both of these trials were conducted more than 30 years ago, and there has been no recent research in Italy to confirm the effects of monophasic NGM/EE in healthy women. Moreover, since then, there has been growing recognition that clinical trials of contraceptives should evaluate a wide range of potential positive and negative impacts for users [19].

Thus, this study is being undertaken to investigate menstrual cycle control during the use of a monophasic COC formulation containing NGM/EE 0.25/0.035 mg (Effimia; Italfarmaco SpA), using established methodologies as well as patient-reported outcomes (PROs).

## Methods

### Recruitment

This prospective, open-label study is being conducted at 6 centers in Italy in healthy women aged 18 to 35 years who are starting oral contraception for the first time or planning to switch to a new COC for the purpose of contraception and not for therapeutic reasons. No specific tests are performed before enrollment, consistent with Italian guidelines that such tests are not indicated in women without individual or family risk factors [20]. Patients who are switching need to undergo a 1-month washout phase prior to entry by discontinuing their previous COC 1 month prior to starting NGM/EE 0.25/0.035 mg. The participants must be residents of Italy and be sufficiently proficient in Italian to understand the informed consent form and the instructions for COC use. The key exclusion criteria are contraindications to the COC according to the current summary of product characteristics, concomitant conditions that place users at risk of AEs, or the use of COC for indications other than contraception, such as polycystic ovarian syndrome, endometriosis, or recurrent menometrorrhagia. Complete inclusion and exclusion criteria are shown in Textbox 1. Certain concomitant medications are not permitted for the duration of the study to minimize the potential for drug interactions or confounding of end-point assessment (Textbox 1).

Complete inclusion and exclusion criteria.
**Inclusion criteria (all must be met)**
Healthy women aged between 18 and 35 years (inclusive) in need of contraception.Residing in Italy and having a good knowledge of the Italian language, such as to correctly understand the informed consent form and the instructions for use and to ensure potential adherence to the study.Willing and able to understand and complete the written informed consent form.Willing to comply with the study protocol.
**Exclusion criteria (any 1 of these disqualifies an individual from participating)**
Any contraindications to the use of combined oral contraceptives (COCs) according to the current summary of product characteristics of Effimia, that is, women presenting (or having ever presented) with myocardial infarction, transient ischemic attack, stroke, angina pectoris, deep vein thrombosis, pulmonary embolism (or presence of blood clots in organs other than legs and lungs), any blood clotting disorder (such as protein C deficiency, protein S deficiency, and antithrombin-III deficiency), or who need to undergo surgery or lie down for a long period of time (including the risk of previous deep vein thrombosis, arterial thromboembolism, hypertension in the course of treatment, and diabetes). If any of the listed conditions should appear during the use of the tested COC, the product must be stopped immediately, and the participant withdrawn from the study.Severe diabetes with blood vessel damage, heart valve disease with complications, severe hypertension, severe hypercholesterolemia or hypertriglyceridemia, hyperhomocysteinemia, migraine with aura, hepatitis C (and taking medications for this condition), endometrial hyperplasia, or unexplained vaginal bleeding.Women who are breastfeeding or pregnant or suspect they are pregnant.Current or history of any liver disease not yet recovered (liver function not yet normalized), any benign or malignant tumor of the liver, any breast or genital organs cancer (even suspected), or jaundice during pregnancy or while using hormonal contraceptives.Galactose intolerance, total lactase deficiency, or glucose-galactose malabsorption syndrome.Hypersensitivity to the active substances or to any excipients of the tested COC (eg, norgestimate, ethinyl estradiol, or lactose).Use of any of the following during the study period (according to the summary of product characteristics of Effimia): treatments for tuberculosis (eg, rifampicin), epilepsy (eg, primidone, phenytoin, barbiturates, carbamazepine, or oxcarbazepine), HIV and hepatitis C virus infection (protease inhibitor drugs and nonnucleoside reverse transcriptase inhibitors such as ritonavir, nevirapine, efavirenz, and also ombitasvir, paritaprevir, or dasabuvir), fungal infections (eg, griseofulvin), arthritis, osteoarthritis (etoricoxib), or pulmonary arterial hypertension (bosentan), and St John's wort used as an antidepressant. Medicines containing cyclosporine, antiepileptic lamotrigine, tranexamic acid, theophylline (used to treat respiratory problems), and tizanidine (used to treat muscle pain or cramps) should not be taken as well.Use of hormonal contraceptives in the previous month.BMI ≥30 kg/m^2^ (class I obesity).Smoking >15 cigarettes per day.Off-label use of COC (eg, for polycystic ovarian syndrome, endometriosis, or recurrent menometrorrhagia).Currently taking part or who took part in clinical studies with experimental products in the previous month.Incapacity or inability to comply with the study protocol (unreliability in the intake of the product or in the completion of the diary) according to the investigator’s opinion.

### Ethics Approval

The study protocol and amendments were approved by the ethics committee at the coordinating center (Territorial Ethics Committee—Liguria; application 202100302715-003), with the latest version approved on June 17, 2024. The study is being conducted in accordance with the Declaration of Helsinki (seventh revision, 2013), the Convention of Oviedo in April 1997 and the additional protocol in January 1998, and the national laws, regulations, and applicable guidelines of Italy. In addition, the study is consistent with the International Conference on Harmonization Tripartite Guidelines for Good Clinical Practice requirements. Prior to any procedures, participants are given information about the study and asked to sign an informed consent form. Their personal data are deidentified before being stored and protected according to the current European General Data Protection Regulations. The women do not receive any financial compensation for participating in the study.

### Procedures

During the baseline visit, participants have a physical examination, including an assessment of acne severity (using the Global Acne Grading Scale [GAGS] [21]), and provide a complete medical and menstrual history (Figure 1). They are asked about the characteristics of their menstrual cycle (frequency, duration, regularity, estimated flow volume, and breakthrough bleeding), any unscheduled bleeding, and an evaluation of dysmenorrhea, using a 100-mm visual analog scale (VAS) from 0=no pain to 100=very severe pain. Participants are also being asked to complete a Profile of Mood State (POMS) to assess premenstrual syndrome and the Female Sexual Function Index (FSFI) to evaluate the quality of their sex life, using the validated Italian language versions of these questionnaires [22-24]. At 1 site (Genoa), 28 participants are also providing a blood sample for the assessment of metabolic, endocrine, and coagulation parameters (Textbox 2).

At the baseline visit, participants are provided with NGM/EE 0.25/0.035 mg for the first 3 cycles and a diary, in which they are asked to record cycle evaluation parameters (Table 1), their medication-taking behavior, concomitant medications including over-the-counter medications (start and stop dates and dose), and any AEs.

Study participants are asked to return to the study site for 2 further visits, at day 84 and day 168 (Figure 1), and to bring their diaries and medication with them (whether used, partially used, or not used). At visit 2, researchers check the diaries to verify that participants are completing them correctly and provide them with new diaries and another 3 cycles of NGM/EE 0.25/0.035 mg. At both visits 2 and 3, the same assessments are conducted as at the baseline visit (physical examination, GAGS, POMS, FSFI, and dysmenorrhea VAS), and participants are asked about concomitant treatments, adherence, and AEs. At visit 3, the diaries are collected for final verification, and the subgroup of participants from Genoa provides another blood sample. In the case of an early withdrawal before the end of the sixth cycle, the investigator asks the participant to return for a final visit and records the reasons for the participant’s decision to discontinue the study.

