### End Points

The primary objective of the study is to investigate menstrual cycle control by evaluating breakthrough bleeding (ie, bleeding or spotting between the cyclically regular onset of menses) during the use of the monophasic NGM/EE 0.25/0.035 mg COC. This is measured by calculating the intermenstrual bleeding or spotting occurrence rate at the sixth cycle and comparing this with the rate at baseline.

Secondary outcomes include the change from baseline at visits 2 and 3 in other parameters of cycle control (frequency, duration, regularity, participant-determined flow volume, and unscheduled bleeding), GAGS score, POMS, FSFI, and dysmenorrhea severity based on the VAS rating. Adherence and contraceptive failure rate over the 6-month study period are also secondary outcomes, as are changes from baseline in the metabolic, hormonal, or coagulation parameters in the subgroup of participants from Genoa. Adherence is being evaluated as a percentage of tablets taken, based on the medication returned by participants at each visit. Contraception failure is defined as the proportion of women who become pregnant during the 6-month study period. The reasons for any contraception failure will be identified and listed (eg, discontinuation or poor adherence).

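### The primary comparison, as described, sets an interview history at baseline against a prospective diary at cycle 6, so a change in measurement method cannot be told apart from a drug effect

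*Protocol article*

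**What the plan says.** The End Points section of the protocol article defines the primary measure as "calculating the intermenstrual bleeding or spotting occurrence rate at the sixth cycle and comparing this with the rate at baseline".

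The Procedures section gives the two sources:

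- **Baseline.** Women "provide a complete medical and menstrual history", and "They are asked about the characteristics of their menstrual cycle (frequency, duration, regularity, estimated flow volume, and breakthrough bleeding".
- **On treatment.** "At the baseline visit, participants are provided with NGM/EE 0.25/0.035 mg for the first 3 cycles and a diary". The diary is where they record the Table 1 cycle parameters, which include breakthrough bleeding. The Abstract gives it a length of six cycles, equal to the two supplies of three cycles of drug.
- **Later visits.** "At both visits 2 and 3, the same assessments are conducted as at the baseline visit (physical examination, GAGS, POMS, FSFI, and dysmenorrhea VAS". The cycle-history interview is not in that list.

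Recruitment says that switchers enter after "discontinuing their previous COC 1 month prior to starting NGM/EE 0.25/0.035 mg", and Textbox 1 excludes hormonal contraceptive use in the previous month. The article does not say whether a switcher's history refers to the washout month or to cycles on the earlier pill. Strengths and Limitations names the lack of a control arm and the short follow-up, but not a difference in measurement method.

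**The concern.** In a single-arm study the before-after difference is the only evidence of effect on the primary endpoint. It can be read as a drug effect only if bleeding is measured in the same way at both times. Two things may differ here.

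- **Mode.** Recall at interview and a prospective diary need not catch the same events, above all light spotting.
- **Window.** The cycle-6 rate covers one cycle. A menstrual history may cover more. Regularity, asked about in the same interview, is classed in Table 1 by the spread between shortest and longest cycle, which a single cycle cannot show.

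A longer window or over-recall at baseline would produce an apparent reduction with no drug effect. Under-recall would hide part of a real one. The planned changes are small enough for modest differences in method to matter: at 175 women they amount to 175 × 0.015 = 2.6 women for breakthrough bleeding and 175 × 0.05 = 8.75 women for spotting.

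**Working it through.** **Inputs from the article (Statistical Analysis).** Breakthrough bleeding is expected to go from 4.5% to 3% (1.5 points) and spotting from 9% to 4% (5 points). The power statement is for breakthrough bleeding, with 175 women and a 1-sided 5% level. The 175 serves here only as the number analysed; whether it gives the stated power is a separate question.

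**Assumptions (not in the article).** No drug effect; a constant per-cycle risk p; independent cycles; baseline counted as any event in k recalled cycles, with k from 1 to 6; or a fixed ratio of recalled to diary-recorded events.

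**1. Window effect.** The baseline rate is 1 − (1 − p)^k, against p in the cycle-6 diary.

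| p per cycle | k = 1 | k = 2 | k = 3 | k = 6 |
|---|---|---|---|---|
| 3% | 3.0% | 5.9% | 8.7% | 16.7% |
| 4% | 4.0% | 7.8% | 11.5% | 21.7% |
| 9% | 9.0% | 17.2% | 24.6% | 43.2% |

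For example, 1 − 0.91³ = 1 − 0.7536 = 24.6%, an apparent fall of 15.6 points with nothing changed.

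**2. Window that reproduces the planned effect with no drug effect.** Solve 1 − (1 − p)^k = baseline rate:

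- Breakthrough bleeding: k = ln(0.955)/ln(0.97) = 1.51 cycles turns 3% into 4.5%.
- Spotting: k = ln(0.91)/ln(0.96) = 2.31 cycles turns 4% into 9%.

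**3. Chance of a significant reduction with no drug effect.** This uses an exact 1-sided McNemar test with n = 175 and discordant probabilities p_b(1 − p) and p(1 − p_b), where p_b is the recalled baseline rate. The paired test is my assumption; the article names only chi-square and Fisher tests for categorical data.

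| p per cycle | k = 1 | k = 2 | k = 3 |
|---|---|---|---|
| 3% | 2.4% | 29% | 69% |
| 4% | 2.8% | 37% | 81% |

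If the window is one cycle but recall over-reports, a ratio of 1.5 at 3% gives 12%, and a ratio of 2.25 at 4% gives 53%.

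**4. Correlated cycles.** If the same women bleed in every cycle, any event in k cycles has the same probability as an event in one, and the window effect is zero. The figures in steps 1 to 3 are therefore the independent-cycle end of a range that starts at no window effect.

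**5. Under-recall, one-cycle window.** At 70% recall, 4.5% reads as 0.7 × 4.5 = 3.15% (1.35 points lost) and 9% reads as 0.7 × 9 = 6.3% (2.7 points lost). At 90% the losses are 0.45 and 0.9 points; at 50%, 2.25 and 4.5 points. To cancel the whole planned change, recall must fall to 3/4.5 = 67% for breakthrough bleeding or 4/9 = 44% for spotting.

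**The case against.** The strongest reply is that the article condenses a fuller protocol. The recall window is case-report-form detail, so its absence here is no fault, and if the form asks about the last cycle only, the window effect is zero. That stands, and the point does not rest on the missing window. A one-cycle window would still leave recall on one side and a diary on the other.

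Second, the list of repeated assessments is a parenthesis, Figure 1 is not shown, and End Points plans change from baseline in other cycle parameters at visits 2 and 3. The article also never says in one sentence that the cycle-6 rate comes from the diary. A reader might infer that no matched pair exists anywhere in the study. The text supports only that none is described; the diary is the only source it describes for cycle 6.

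Third, a reader might infer a bias larger than the planned effect in either direction. The working does not support that as a general statement. At 70% recall the loss exceeds neither matching planned effect (1.35 against 1.5 points, 2.7 against 5), and under-recall works against finding a reduction.

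Fourth, a reader might take the washout month as the natural baseline for switchers. That would make permanent a difference between them and first-time users, and the article does not say what their history covers.

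**Conclusion.** The concern holds in this form: as described, baseline is an interview history and cycle 6 is a prospective diary begun with treatment. With no control arm, the design cannot separate a difference in method from a drug effect. The description of the instruments rests on the Abstract, Procedures and End Points.

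The size is not known. A window of about 1.5 or 2.3 cycles would be enough to mimic the planned breakthrough-bleeding or spotting effect, if cycles are independent and the drug does nothing. The 15.6-point fall is one scenario (three recalled cycles, independence, a 9% rate), to be set beside the 5-point spotting effect and not the 1.5-point effect for which power is stated. It is not an estimate of bias in this trial. The direction is open too: a long window or over-recall favours a false reduction, and under-recall conceals a true one.

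This is a cheap and worthwhile correction, not a ground for setting the study aside.

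**What to change.** - Define the baseline item as the last complete cycle before the first tablet, for every woman.
- At visit 3, ask the identical structured question about cycle 6, before the diary is reviewed.
- Prespecify the recall-to-recall change as a supporting analysis beside the diary-based comparison.
- Report the cycle-6 diary rate with its confidence interval.
- Show results separately for first-time users and switchers, as a descriptive check.
- Name the difference in instruments as a limitation beside the missing control arm.

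The cost is one question at an existing visit, a tighter baseline item and some analysis wording. Women who have already finished will lack the visit 3 answer. How many can still be asked depends on the timetable: the Abstract expects enrollment to end in December 2024, the Results section in December 2025 with the last visit in June 2026. Visit 3 recall also follows six cycles of diary keeping, so it is closer to the baseline history but not fully equivalent. For finished women, the diary rate with its interval, the split by prior use and the stated limitation remain available.

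I would not issue the diary a cycle earlier to women still to be enrolled. It needs contact and consent before the present baseline visit, and it would mix two baseline instruments within one primary endpoint.
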